## Abstract

**Background:**

Geriatric diseases (e.g., chronic diseases and geriatric syndromes) may result in impaired physical performance and a decline in the quality of life. The results of previous studies reported the positive effects of comprehensive community-based rehabilitation (CBR) services on physical and social functioning and psychosocial wellbeing. However, to provide adequate and personalised rehabilitation services, it is essential to understand the needs of the older adults population. There have been no studies on the need for CBR in older adults populations that consider their heterogeneity. Therefore, high-quality studies are required to recognise the heterogeneity and latent classes of CBR needs in older adults population groups. This study aims to identify the heterogeneity of the rehabilitation needs of older adults in the community and explore whether older adults with similar characteristics have similar needs through a cross-sectional survey and latent class analysis (LCA) to provide support for personalised rehabilitation services.

**Methods:**

The study is structured into four phases. The first phase will focus on constructing a comprehensive questionnaire to assess rehabilitation needs. In the second phase, a pilot study will be conducted to evaluate the reliability and validity of the completed questionnaire. This step ensures the robustness of the instrument for data collection. The third phase will involve cross-sectional surveys using the finalised questionnaires to collect the necessary data from the targeted population. The fourth phase will focus on conducting LCA to determine the CBR needs of the older adult population.

**Discussion:**

The results of this study will provide novel and critical information for a better understanding of the rehabilitation needs, potential categories, and influencing factors of older adults in the community. The study will be conducted in Guizhou Province in western China, where economic and social development is relatively low, and the results will inform and benefit other regions and developing countries facing similar challenges. However, because of the complete social security and rehabilitation service systems in developed areas, our research results may not fully reflect the situation in these areas. Future studies may need to be conducted in places with different levels of social development.

**Clinical trial registration:**

https://www.chictr.org.cn/showproj.html?proj=191398, ChiCTR2300071478.

## Introduction

1

### Background

1.1

Population ageing is accelerating worldwide, and this demographic transition presents a formidable challenge in managing global public health policies. In China, the estimated older population is expected to increase from 267 million in 2021 to 400 million in 2035, constituting 30% of the total population (1). As people age, their functional performance and intrinsic abilities decline (2), leading to an increased occurrence of chronic illnesses, geriatric syndromes, and multiple medical and psychosocial conditions (3). Studies in China have indicated that the prevalence of chronic diseases in older adults is 69.13% (4), with multiple chronic diseases, pain, mobility disorders, and depressive disorders occurring in 45.5% (5), 30% (6), 19.6% (7), and 36.8% (8) of older adults, respectively, which can profoundly influence their health status and quality of life (9). These findings indicate the importance of offering rehabilitation services to older adults to support their physical, psychological, and social wellbeing.

Among the many forms of rehabilitation service delivery, community-based rehabilitation (CBR) is an effective strategy that addresses disability, rehabilitation, equalisation of opportunities, poverty reduction, and social inclusion of older adults (10). This approach not only offers convenience and feasibility but also preserves older people’s existing social networks, diminishes medical costs, and is widely embraced by this demographic (11, 12). In this process, the success of CBR can be gauged by how well the community can provide customised rehabilitation services for senior citizens (13–15). To achieve this, it is crucial to correctly understand their rehabilitation needs. However, current studies focused on understanding the rehabilitation of individual diseases or repeatedly investigating the overall rehabilitation needs of the entire older adults population and, based on this limited information, used the same method to guide CBR in the older adults population (16–18). Meanwhile, because rehabilitation needs tend to co-occur and heterogeneity exists within a population, a single-need assessment of rehabilitation services is unsuitable for older adults with multiple chronic diseases or various physiological, psychological, and social conditions. Moreover, owing to individual differences and heterogeneity, the scientificity and rationality of providing the same CBR services to older adults need to be verified. Hence, the description of the complete picture of the CBR needs of the older adults population needs to be explored to provide personalised CBR services based on different CBR need subtypes in older adults individuals or groups.

Latent class analysis (LCA) is an effective tool for understanding the overall needs for CBR in older adults and identifying the different CBR need subtypes. LCA describes population heterogeneity in terms of differences across individuals in a set of behaviours or characteristic statistical methods, which is called the person-centred approach (19). Owing to these advantages, it has been used in many fields, such as medicine, sociology, and psychology (20–22), to identify unobserved subgroups, especially potential needs types (23–25). Using LCA, researchers may be able to categorise the CBR needs of older adults into different latent categories and make each category representative of the rehabilitation needs of people with similar characteristics. At the same time, if researchers add covariates, they can also obtain a clearer picture of the factors that influence the CBR needs of older adults. To the best of our knowledge, no LCA studies have been conducted to determine the needs of older adults with CBR.

This study aims to fill existing gaps by conducting a cross-sectional study of the CBR needs of older adults in China and using LCA to elucidate the CBR needs of older adults, including the different need subtypes and influencing factors for this population. The results of this study will positively impact the formulation of targeted CBR policies for older adults and the provision of personalised CBR services.

### Theoretical framework

1.2

Generation of the CBR needs for older adults stems from their functional performance and intrinsic abilities. To enhance our understanding of the CBR needs of older adults, we have integrated three theoretical frameworks: International Classification of Functioning, Disability, and Health (ICF) (26), Guidelines for Community-Based Rehabilitation, and Behavioural Model of Health Services Use (BMHSU) to guide our study (Figure 1). Based on the ICF, we can analyse the physical, psychological, social, and environmental rehabilitation needs of older adults. By establishing a needs assessment mechanism based on the ICF, we laid the foundation for developing a comprehensive CBR implementation plan (27). Simultaneously, to better understand the rehabilitation needs of the older population at the community level, we implemented the Guidelines for Community-Based Rehabilitation. Combining this guide with the ICF can help us understand and explore the CBR needs of older populations from various perspectives, which results in the most critical component of our theoretical framework (Figure 1): diverse rehabilitation needs.

**Figure 1 fig1:**
[figure not shown]
Theoretical framework of multiple needs for community-based rehabilitation in older adults based on the latent class model.

To better understand the factors affecting the CBR needs of older adults, we introduced BMHSU, a classical theoretical model in the field of public health. This model explores the relationship between individual factors and health services (28), elucidating intricate interactions among contextual characteristics, individual characteristics, health behaviours, and health outcomes. Successfully applied in studying older adults’ inclinations toward institutional care, utilisation of long-term care services, community health management, and utilisation behaviour, BMHSU provides valuable insights into individuals’ demand for health services (29–31). Based on the four dimensions offered by BMHSU, we will explore the factors that affect the CBR needs of older adults through a practical setting of influencing factors. Integrating these three theories enables a comprehensive understanding of the CBR needs of older adults, a perspective considering diverse needs categories and influencing factors.

### Study questions

1.3

This study hypothesises that older adults have physiological, psychological, and social participation and environmental and information needs in CBR. Since older adults have multiple needs at the same time, there may be several fixed combinations of these needs in the older adults population (e.g., “Physiological-psychological” combination, “socially-participation-environment” combination). Each older adults person will fall into one of these categories, and contextual characteristics, individual characteristics, health behaviours, and health outcomes influence these combinations.

We aim to address the following three research questions: (i) When older adults individuals have multiple rehabilitation needs, is it more likely that these needs will be combined in a specific manner rather than randomly? (ii) Do older adults with similar characteristics have similar needs? (iii) What key factors are associated with the needs of older adults with multiple CBR needs?

## Methods

2

This study will be a cross-sectional survey guided by our incorporated theoretical framework. This sequential exploratory mixed-methods study is categorised into four phases (Figure 2), which are as follows:

**Figure 2 fig2:**
[figure not shown]
The flowchart describes the main results and critical approaches of the two parts of the current study.

The first part is the development of CBR for older adults’ rehabilitation needs questionnaire, and the first phase will be the development of older adults’ CBR needs questionnaire based on our theoretical framework. This phase includes a literature review, semi-structured interviews, and the Delphi method. The second phase will be a pilot study to verify the older adults’ CBR needs questionnaire and will include validation of the other measurement scales used in this study. This order is commonly employed for questionnaire preparation and verification (32–34).

The second part will involve collecting sufficient data to conduct LCA through a cross-sectional study design. The third phase is the main study, mainly a cross-sectional survey based on the questionnaire used in the pilot study to help us obtain the data needed for LCA. The fourth phase will be LCA, which aims to identify the diversity of older adults’ CBR needs, uncover latent relationships, and determine the factors influencing their needs.

### Phase 1 development of older adults’ CBR needs questionnaire

2.1

#### Literature review

2.1.1

First, to determine the possible dimensions and items in the scale, we will review the literature extensively to better understand the relevant literature and study status affecting the rehabilitation needs of older adults in community-based settings. Literature on the rehabilitation needs of community-dwelling older adults will be searched through PubMed, Embase, Web of Science, CENTRAL, CINAHL, Physiotherapy Evidence Database, CNKI, and other databases. The key search terms will include a combination of “Aged/Elderly/Older adults/Older persons/Aged people/Older adult,” “Community rehabilitation/CBR/Community-based rehabilitation/Home rehabilitation,” and “Need/Demand/Requirement.” The studies included should focus only on the CBR needs. Duplicate publications, studies that did not separate the range of the qualitative data, and non-English or Chinese studies will be excluded. Based on a comprehensive review of the existing literature combined with our theoretical framework, we will construct a questionnaire on body function rehabilitation, mental function rehabilitation, individual activities, social participation, and environmental rehabilitation. Researchers have developed an information needs module to understand the needs of older adults and help them integrate into the community. This module combines content from the Guidelines for Community-Based Rehabilitation (10) and the ICF environment module to reduce the impact of the digital gap. The goal is to implement rehabilitation services through inclusive community development. The primary item pool of the needs questionnaire is shown in Table 1.

**Table 1 tab1:** The needs questionnaire preparation indicators.

Primary index	Secondary index	Category description (ICF code and name)
Body function	Vision and related functions	b210 Visual functions b215 Functions of structures adjoining the eye b220 Sensations associated with the eye and adjoining structures
	Hearing and vestibular functions	b230 Hearing functions b235 Vestibular functions b240 Sensations associated with hearing and vestibular function
	Pain	b280 Sensation of pain
	Voice and speech functions	b310 Voice functions b320 Articulation functions b330 Fluency and rhythm of speech functions b340 Alternative vocalisation functions
	Heart functions	b410 Heart functions
	Functions of the respiratory system	b440 Respiration functions b445 Respiratory muscle functions
	Swallowing function	b510 Ingestion functions
	Defecation functions	b525 Defecation functions b620 Urination functions
	Weight maintenance functions	b530 Weight maintenance functions
	Functions of the joints and bones	b710 Mobility of joint functions b715 Stability of joint functions b720 Mobility of bone functions
	Muscle functions	b730 Muscle power functions b735 Muscle tone functions b740 Muscle endurance functions
	Movement functions	b750 Motor reflex functions b755 Involuntary movement reaction functions b760 Control of voluntary movement functions b765 Involuntary movement functions b770 Gait pattern functions
Mental functions	Cognitive function	b110 Consciousness functions b114 Orientation functions b140 Attention functions b144 Memory functions b164 Higher-level cognitive functions
	Sleep functions	b134 Sleep functions
	Psychomotor functions	b147 Psychomotor functions
	Emotional functions	b152 Emotional functions
Individual activities	Changing and maintaining body position	a410 Changing basic body position a415 Maintaining a body position a420 Transferring oneself
	Carrying, moving, and handling objects	a430 Lifting and carrying objects a435 Moving objects with lower extremities a440 Fine hand use a445 Hand and arm use
	Walking and moving	a450 Walking a455 Moving around a460 Moving around in different locations
	Self-care	a510 Washing oneself a520 Caring for body parts a530 Toileting a540 Dressing a550 Eating a560 Drinking a570 Looking after one’s health
Social participation	Interpersonal interactions	p710 Basic interpersonal interactions p720 Complex interpersonal interactions
	Interpersonal relationships	p730 Relating with strangers p740 Formal relationships p750 Informal social relationships p760 Family relationships p770 Intimate relationships
	Community life participation	p910 Community life
	Recreation and leisure	p920 Recreation and leisure
Environment	Use of assistive devices	e115 Products and technology for personal use in daily living e120 Products and technology for personal indoor and outdoor mobility and transportation e125 Products and technology for communication
	Cultural and entertainment	e140 Products and technology for culture, recreation, and sport
	Barrier-free environment transformation	e150 Design, construction and building products, and technology of buildings for public use e155 Design, construction and building products, and technology of buildings for private use
Information	Social security and public service information	e545 Civil protection services, systems, and policies e575 General social support services, systems, and policies
	Health-related information	e580 Health services, systems, and policies
	education and training information	e585 Education and training services, systems, and policies
	Laws and policies protect relevant information	e550 Legal services, systems, and policies e595 Political services, systems, and policies
	Social engagement or empowering information	e555 Associations and organisational services, systems, and policies e560 Media services, systems, and policies

#### Semi-structured interviews

2.1.2

Semi-structured face-to-face interviews will be conducted with older adults individuals with CBR needs to ensure the alignment of items with their respective dimensions and generate valid measurements (35). Participants will be selected through purposeful sampling, adhering to specific criteria for inclusion in the interviews: (1) age ≥ 60 years, (2) either currently undergoing or on the verge of receiving such services, (3) the ability to self-report, characterised by sufficient language understanding and expression skills, and (4) received informed consent from both participants and their families to willingly participate in the study. Sample size will be determined following the principle of data saturation, with an estimated requirement of approximately 20–25 respondents to achieve information saturation. In instances where saturation is uncertain, supplementary interviews will be conducted (36). Two trained individuals will interview each participant at their chosen location. Written informed consent will be obtained before each interview, and the interview sessions will be recorded for an average duration of approximately 30 min.

Participants will be queried on various aspects, including (1) How is your health now? (2) What inconveniences will you encounter during CBR? (3) What are your needs when receiving CBR services? (4) What challenges do you expect when receiving community CBR services? (5) What exceptional help do you require? and (6) What are your suggestions for improving CBR services?

The interview recordings will be transcribed into Word documents for subsequent analyses. Employing the Colaizzi content analysis method, the two researchers will analyse, summarise, encode, compare, confirm, and refine the emergent themes. The questionnaire items will be supplemented based on the results of the qualitative research combined with the primary entry pool.

We will filter our pool of entries based on a literature review and semi-structured interviews to form the first draft of our questionnaire, which will be screened and supplemented by a Delphi study.

#### The Delphi method

2.1.3

The Delphi method is intended to score and guide the importance and feasibility of constructing an older adult’s CBRN-Q (37).

The researchers will first establish an expert group that includes rehabilitation medicine doctors, geriatric medicine experts, geriatric nurses, and rehabilitation nursing experts. Members of this team must have >10 years of clinical experience and intermediate or higher professional titles. More than 15 experts will be involved in this stage (38).

The survey will include an expert letter questionnaire conducted via e-mail correspondence, a questionnaire that includes the study background, an expert general situation questionnaire, and the main body of the questionnaire. The expert will evaluate the importance (rated on a Likert scale from very important, 5, to unimportant, 1) and feasibility (very low to too much) of each item in the CBR needs questionnaire for older adults. The researchers will summarise, screen, and modify the opinions put forward by experts on older adults’ CBR needs questionnaire items, request the experts for consultation again, and repeat the process until the experts stop contributing their opinions (39). Entries that meet the following criteria will be retained: the mean value of the importance assignment X > 3.5 and the coefficient of variation (CV) < 0.25 (40).

Finally, the research group will discuss expert opinions and suggestions to further improve the older adults’ CBR needs questionnaire. Simultaneously, since the core of the study is the model construction and analysis based on LCA, there should be a clear boundary value for both the scale and items used so that the data can be easily converted into binary variables for analysis.

### Phase 2 pilot study

2.2

#### Study sample and sample size

2.2.1

Using purposive sampling, we will conduct a questionnaire survey on older adults in Zunyi, Guizhou Province. The sample size for questionnaire verification should be 10 times the number of questionnaire items (41). Because the questionnaire we developed is estimated to have 40–45 items, we will need at least 450 participants. Considering a 10% loss to follow-up rate, we determine that the sample size of the pre-trial is 500 participants.

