##### Validity analysis

2.2.4.2

Exploratory factor analysis (EFA) and confirmatory factor analysis (CFA) will be used to assess the construct validity of the CBRN-Q. The collected samples will be randomly categorised into two independent subsets for EFA and CFA.

Before performing the EFA, we will test whether the data can be factor-analysed using Bartlett’s sphericity test and the Kaiser–Meyer–Olkin (KMO) test. The probability of Bartlett’s Test of Sphericity <0.05 or KMO >0.7 indicates that EFA can be performed (46). We will perform EFA using principal component analysis, oblimin rotation, and parallel analysis. We will keep entries with an item factor load >0.4 and no more than one factor (47, 48).

CFA will verify the factor structure of the CBRN-Q based on maximum likelihood estimates. CFA will use three indexes: comparative fit index (CFI), root-mean-square residual (SRMR), and root-mean mean-square error of approximation. CFI value ≥0.90 indicates an acceptable model fit, and ≤ 0.08 indicates a good fit; similarly, SRMR value ≤0.08 indicates a good fit (46).

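### The pilot is sized at 10 respondents per item on the undivided sample, but splitting it for EFA and CFA leaves about 5 to 6 per item for each factor analysis

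*Protocol article*

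**What the plan says.** Section 2.2.1 of the Protocol article sets the pilot size in four steps:

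- The rule: "The sample size for questionnaire verification should be 10 times the number of questionnaire items".
- The item count: "the questionnaire we developed is estimated to have 40–45 items".
- The minimum: "we will need at least 450 participants".
- The allowance and result: "Considering a 10% loss to follow-up rate", and then "we determine that the sample size of the pre-trial is 500 participants".

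Section 2.2.4.2 describes the validity work: "Exploratory factor analysis (EFA) and confirmatory factor analysis (CFA) will be used to assess the construct validity of the CBRN-Q". It continues: "The collected samples will be randomly categorised into two independent subsets for EFA and CFA". It gives no split ratio, and no size or per-item target for either part. The same section keeps an item if it loads above 0.4 and on no more than one factor.

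Section 2.2.4.1 tests internal consistency by Cronbach's alpha and does not tie that analysis to the split.

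**The concern.** The per-item rule is the only reason given for 450 and 500. EFA and CFA are the only validity analyses that the pilot describes, and neither can use the whole sample. A reader of 2.2.1 would take it that the factor analyses rest on ten respondents per item. On the plan in 2.2.4.2, they rest on roughly half that.

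What is at stake is how firmly the pilot can decide which items to keep. That decision uses a fixed loading cut-off, so an item near 0.4 may fall on either side by chance, and more easily with fewer respondents. If standard errors scale with one over the square root of the sample size, going from 450 to 225 respondents multiplies them by √(450/225) = √2, about 1.4. The protocol should say what precision it actually has for this step.

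**Working it through.** **Inputs.** From 2.2.1: 10 respondents per item, 40 to 45 items, a minimum of 450, a 10% loss, and 500 planned. From 2.2.4.2: two separate subsets, one for each factor analysis. Assumed, because the protocol does not say: an equal split.

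**The plan's own figure.**
- Completers needed: 10 × 45 = 450.
- Recruits needed: 450 / (1 − 0.10) = 500. This matches exactly.

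**Before the split**, respondents per item = N / items:
- 450 / 45 = 10.0
- 500 / 45 = 11.1

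The rule is met on the undivided sample.

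**After an equal split**, respondents per item = (N / 2) / items:

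| Completers | Per subset | 45 items | 40 items |
|---|---|---|---|
| 450 (10% lost) | 225 | 5.0 | 5.6 |
| 500 (none lost) | 250 | 5.6 | 6.25 |

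The EFA runs on the full item set, so its ratio is 5.0 to 6.25 across the protocol's own range.

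**The CFA after items are dropped.** The CFA may carry fewer items than the EFA, so the ratios above are its lower bounds. To reach 10 per item:
- 225 / 10 = 22.5, so 22 or fewer items must remain.
- 250 / 10 = 25, so 25 or fewer items must remain.

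With 45 items at the start, that means losing about half of them.

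**Does an unequal split help?** Ten per item in both subsets on the full item set needs 2 × 10 × items completers: 900 for 45 items, or 800 for 40. Both exceed 500, so no ratio works.
- 450 completers, 45 items: giving one subset 10 per item uses all 450 and leaves none.
- 500 completers, 40 items (the most favourable case): giving one subset 400 leaves 100, and 100 / 40 = 2.5 per item.

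**Size needed to meet the rule in both subsets.**
- 45 items: 900 completers, 900 / 0.9 = 1,000 recruited.
- 40 items: 800 completers, 800 / 0.9 = 888.9, so 889 recruited.

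**The case against.** The strongest reply is that the rule is worded for verification as a whole, and the total sample meets it. The protocol never promises ten per item within each factor analysis. Whether the cited source intends that cannot be checked here. This much stands: the figures are right, and an analysis on all respondents, such as Cronbach's alpha, has its ten per item. The reply does not remove the mismatch. Construct validity is a main part of verification, it is assessed only on the subsets, and the sizing passes over that.

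Two further replies have partial force. The equal split is an assumption, though no other ratio serves both analyses. Items dropped at the EFA raise the CFA ratio, but this gives the EFA no relief.

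A reader might infer more than the protocol supports:

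- *That the sample size is miscalculated.* It is not; 450 and 500 both reproduce.
- *That 5 to 6 respondents per item is too few.* Nothing in the protocol shows that 225 to 250 respondents would give unstable loadings. The point is only that the stated justification does not describe the analyses as planned.
- *That weak item selection passes directly into the latent classes.* Section 2.4 classes people by six types of need, and 2.1.3 speaks of cut-offs for the scale as well as for items. It is not settled that single retained items are the indicators, so this carry-over is not established.

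**Conclusion.** The sizing basis in 2.2.1 and the analysis in 2.2.4.2 do not match. Assuming equal halves and 40 to 45 items, the EFA has 5.0 to 6.25 respondents per item. The CFA starts from the same range and rises only as items are removed. The finding that both analyses cannot reach ten per item on the full item set does not depend on the split ratio. This is an inconsistency between a rationale and a plan. It is not an arithmetic error, and it does not show that the pilot is too small for its purpose. It is worth correcting because the per-item figure is the whole of the stated justification, and the correction is cheap.

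**What to change.** - In 2.2.4.2, state the split ratio.
- In 2.2.1, restate the justification: about 5 to 6 respondents per item for each factor analysis if the halves are equal, and 10 per item only for reliability on the whole sample.
- Describe how precisely a loading near the 0.4 cut-off will be estimated with 225 to 250 respondents.

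This changes wording and adds a short precision statement. It needs no extra recruits and no change of sequence.

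Enlarging the pilot to about 1,000 recruits would deliver ten per item in both halves at 45 items. It would double recruitment and is not proposed.

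Repeating the CFA on Phase 3 respondents could serve as an optional supplementary check. It should not replace the pilot CFA, because confirmation would then come only after the questionnaire had been fielded. The samples also differ: the pilot is a purposive sample from Zunyi (2.2.1), whereas Phase 3 is a province-wide cluster sample (2.3.3). A repeat CFA would have to allow for that clustering.
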